### Baseline Testing and Randomization

Baseline testing will last approximately 150 minutes. Participants will be provided with a detailed consent form and will be invited to ask any questions. After written consent is obtained, weight, height, and blood pressure will be taken and a 7-day physical activity recall interview [44] will be conducted to confirm eligibility.

Eligible individuals will be stratified based on sex and then randomly assigned to either the HIIT or MICT exercise conditions. An external statistician, who has no other involvement in the trial, will generate random allocation sequences, which will be linked to an interactive Web page. Permuted blocks of random size will be used. Once an individual is identified as eligible, the research coordinator will access the password-protected Web page, and after entering requisite information on patient eligibility and sex, participants will be randomly allocated. Participants and researchers will be aware of group allocation. Following group assignment, participants will have a fasting blood sample taken, consume a 75 g glucose drink as part of a modified oral glucose tolerance test, complete several Web-based questionnaires, have a second blood sample taken 30 minutes following the glucose drink consumption, undergo a body composition scan, and complete a maximal cardiorespiratory fitness test to exhaustion on a cycle ergometer. At the end of the session, participants will be provided with an accelerometer to wear for 7 consecutive days, commencing the day after baseline testing. Participants will be shown how to wear the device and will be instructed to remove the device while sleeping or for water-based activities. In addition, instruction will be provided to remind participants how to correctly wear the accelerometer. Short message service (SMS) text messages or emails will be sent on days 1, 3, and 5 of monitoring to remind participants to wear the device (see Multimedia Appendix 1 for study measures).

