#### Secondary Outcomes

##### Physical Activity

Objectively measured purposeful MVPA adherence (ie, MVPA10+) will be assessed by triaxial accelerometry (Actigraph GT3X-BT, Actigraph, Pensacola, Florida, USA) at baseline and 3-, 6-, 9-, and 12-month follow-up. MVPA10+ is appropriate for measuring purposeful exercise [51] and provides a conservative estimate of exercise adherence. Participants will be instructed to wear the accelerometer on their right hip for 7 consecutive days at each measurement time point. Participants will be instructed to remove the accelerometer during sleep and for water-based activities. Accelerometers will be initialized and downloaded using ActiLife version 6.11. Epoch lengths will be specified at 5 seconds and will be summed as counts per minute. Nonwear time will be classified as 90 minutes of consecutive zeros, allowing for nonzero counts up to 2 minutes; if no counts are detected during the 30-minute counts before and after this interval [52], these data will be classified as nonwear time and excluded from analysis. Participants must have a total of ≥10 hours of valid wear time per day to be included in the analyses [53]. Our pilot work confirmed that recovery intervals during HIIT register as moderate-to-vigorous activity, not interruptions to physical activity. Freedson cut points [54] will be used to identify time spent in moderate (1952-5724 counts/min), vigorous (≥5725 counts/min), and MVPA (≥1952 counts/min) during wear time on valid wear days. Time spent in the various intensities will be averaged across valid wear days and multiplied by 7 to provide a weekly estimate of physical activity at each measurement time point. Purposeful exercise will be operationalized as minutes spent in MVPA10+ [54], in line with physical activity guidelines, which specify that bouts of physical activity should be accumulated in bouts of 10 minutes or more. Furthermore, given that participants in HIIT are prescribed 75 minutes of purposeful exercise per week (ie, 3×25-min HIIT sessions) and participants in MICT are prescribed 150 minutes per week (ie, 3×50-min MICT sessions) and that physical activity guidelines highlight the equivalency of 75 minutes of vigorous exercise and 150 minutes of moderate exercise, additional supplemental analyses will be conducted, whereby each vigorous minute of exercise within the identified MVPA10+ bouts will be credited as 2 minutes. This approach was carefully considered for the adherence measure and justified in the grant application for this trial. As such, this modified MVPA10+ outcome represents an appropriate measure of purposeful exercise [51] and allows for a direct assessment of adherence to HIIT or MICT.

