#### Proposed Data Analyses

Preliminary analyses will be conducted to test for univariate and multivariate outliers and to test for normality. Data transformations will be conducted if required. Variance between the conditions in baseline outcome variables will be examined. Data will be analyzed on an intention-to-treat basis, with individuals retained within their randomized groups regardless of participation. All significance tests will be assessed at a 5% level of significance and effect sizes will be reported. Sensitivity analysis will be conducted to examine the impact of missing data. We will account for missing data by performing multiple imputation by chained equations to determine whether the results are impacted [74].

Mixed-effects regression with baseline as a covariate and 6- and 12-month outcomes as dependent variables will be used to examine differences in cardiorespiratory fitness between HIIT and MICT. Physical activity behavior assessed by accelerometer will be analyzed similarly but will include 3-, 6-, 9-, and 12-month time points. Mixed-effects regression using baseline and all other time points will be used to determine whether the treatments result in a significant change from baseline.

The mediating effects of task self-efficacy, self-regulatory efficacy, concurrent self-regulatory efficacy, outcome expectations, and self-monitoring will be examined using the INDIRECT macro developed by Preacher and Hayes [75]. The macro computes the following steps simultaneously: (1) regression coefficients for the impact of the intervention on the potential mediators; (2) the association between changes in the mediators and changes in the outcome variable; and (3) the total effects, direct effect, and indirect intervention effects. Bias-corrected bootstrapped 95% asymmetrical CIs will be computed for the indirect effect. Significant mediation will be established if the CIs do not include zero. Multiple mediation models will be computed for MVPA at 12-month follow-up and cardiorespiratory fitness at 12-month follow-up.

A series of mixed-effects regressions will be conducted to examine changes over time between groups in anthropometrics, body composition, biochemical markers, CGM, and additional psychological constructs.

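### The main between-arm models omit any randomised participant without a baseline value, which matters mainly for accelerometry, and imputation is described only as a sensitivity check

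*Protocol article*

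**What the plan says.** Four statements in the protocol article, Proposed Data Analyses, bear on this.

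- The fitness comparison: "Mixed-effects regression with baseline as a covariate and 6- and 12-month outcomes as dependent variables will be used to examine differences in cardiorespiratory fitness".
- Activity: "Physical activity behavior assessed by accelerometer will be analyzed similarly but will include 3-, 6-, 9-, and 12-month time points".
- A further model, for change over time: "Mixed-effects regression using baseline and all other time points will be used to determine whether the treatments result in a significant change from baseline".
- The analysis population: "Data will be analyzed on an intention-to-treat basis, with individuals retained within their randomized groups regardless of participation".

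On missing values the same section says "Sensitivity analysis will be conducted to examine the impact of missing data", followed by "We will account for missing data by performing multiple imputation by chained equations to determine whether the results are impacted".

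Baseline Testing and Randomization puts allocation before the baseline blood samples, body scan, fitness test and accelerometry, and states that participants and researchers know the allocation. The device comes last: "participants will be provided with an accelerometer to wear for 7 consecutive days, commencing the day after baseline testing". The Physical Activity section adds the wear rule: "Participants must have a total of ≥10 hours of valid wear time per day to be included in the analyses". Activity is then averaged over valid days. No minimum number of valid days is stated.

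Mediation uses the INDIRECT macro, relating changes in the mediators to changes in the outcome, for 12-month MVPA and 12-month fitness. The text does not say how missing values are treated there.

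**The concern.** Likelihood-based mixed models use every outcome that was observed, so missing follow-ups need not remove a person. A missing covariate does remove the person unless it is imputed. With baseline on the right-hand side, someone with valid activity weeks at 3, 6, 9 and 12 months but no valid baseline week contributes nothing to the main arm contrast.

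Usually baseline precedes randomisation, so such losses cannot depend on the arm. Here the baseline activity week follows an allocation the participant knows. Entry to the main activity analysis can then depend on behaviour after randomisation. At stake are some precision and, if failure to wear the device differs by arm in a way related to activity, some bias.

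Mediation has a related gap. A change score needs both a baseline and a follow-up value, so without imputation anyone missing either cannot enter those regressions. The plan itself expects about 20% loss to follow-up.

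**Working it through.** **1. The plan's own figure.** Sample Size gives 41 per group for 10 min/day, SD 16, 80% power, two-sided 5%. The two-means formula gives 2 × [16 × (1.960 + 0.842)/10]² = 40.19, rounded up to 41, so the figure reproduces. It is used here only to set the scale: 50 randomised per arm with 20% loss leaves 50 × 0.80 = 40.

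**2. Who is kept.** In simulated data with 100 randomised, 5 baselines set to missing and no imputation, the baseline-as-covariate model keeps 95 people. A model with baseline as one of the outcomes keeps all 100.

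**3. Cost in precision.** The share of missing baselines, q, is not in the document; 0–15% is assumed. The correlation r = 0.5 is the plan's value for VO2 peak, borrowed here for activity.

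For one follow-up, in units of the outcome variance, a person with a baseline carries information 1/(1 − r²) = 1/0.75. A person without one carries 1. With n₁ = 40(1 − q) and n₀ = 40q:

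SE ratio = √[(n₁/0.75 + n₀)/(n₁/0.75)]

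| q | n₁ per arm | n₁/0.75 | n₀ | SE ratio |
|---|---|---|---|---|
| 0% | 40 | 53.33 | 0 | 1.000 |
| 5% | 38 | 50.67 | 2 | 1.020 |
| 10% | 36 | 48.00 | 4 | 1.041 |
| 15% | 34 | 45.33 | 6 | 1.064 |

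For the average of four follow-ups, all correlated 0.5, the variance is (1 + 3 × 0.5)/4 = 0.625, or 0.625 − 0.25 = 0.375 after adjustment. At 15% missing the ratio is √[(34/0.375 + 6/0.625)/(34/0.375)] = √(100.27/90.67) = 1.052. Simulation of the two models gave a difference of about 3–7% at 5–15% missing. About 0–7% covers all of these.

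**4. Mediation.** Assume a mediator–outcome correlation of 0.3, 20% dropout, and dropout odds ratios of 2.7 or 7.4 per SD. These are illustrative values.

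- Dropout driven by an earlier, observed activity value that correlates 0.5 with the 12-month outcome: the complete-case slope shrinks by about 4–9%. The size depends on how strongly the mediator correlates with the earlier value: about 2–6% at 0.15 and 5–10% at 0.3. Imputation that includes the earlier value removes this.
- Dropout driven by the unobserved 12-month value itself: the slope shrinks by about 10% and 22%. Imputation with the earlier value leaves ratios of only about 0.91 and 0.82, so it removes little of the bias.

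**The case against.** The other side has several good points.

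- **Intention-to-treat.** A reader might infer that the promised intention-to-treat analysis is not delivered. The document does not support that. It defines the term by group membership, plans multiple imputation that can fill missing baselines, and names a model that includes baseline among the time points.
- **Primary outcome.** Baseline VO2 peak is measured at the allocation visit, so few values should be missing.
- **Rate.** The wear rule applies to days, with no stated minimum number of days. As written, a baseline is lost only when no day is valid, and reminders go out on days 1, 3 and 5. The true rate may lie near 0%.
- **Power.** An unadjusted two-sample test at one time point would suggest a marked power loss. That is not the planned model. For one baseline-adjusted time point at r = 0.5, power for 10 min/day goes from about 89% with no missing baselines to 83% at 15%. For the average of four follow-ups it stays near 99%. The 10 min/day is in any case set as a within-condition target.
- **Mediation.** The document does not say the macro will be run on complete cases, and does not rule out imputed data. Mediation is explanatory, not the randomised comparison.
- **Equal baseline means.** If knowing the arm alters baseline wear or activity, constraining the arm means to be equal is wrong. True, but covariate adjustment has the same weakness: a spurious baseline difference δ enters the contrast as −rδ. With r = 0.5 and δ = 0.2 SD that is −0.10 SD. In simulation the bias was −0.10 for both models.

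All but the last limit the size of the point. None removes it: the stated main model drops people without a baseline, and imputation is worded as a check.

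**Conclusion.** The point holds in a limited form. As written, the main between-arm models exclude randomised participants without a baseline value, and the planned imputation is placed in a sensitivity role. The practical exposure is accelerometry, where baseline is collected at home after open allocation. For VO2 peak it should be slight.

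The precision cost is about 0–7% in the standard error, for an assumed 0–15% of missing baselines and r near 0.5. Bias arises only if the missingness is informative, and nothing in the document allows its size to be estimated.

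For mediation, the gap is that the text does not provide for imputed data in the main run. The gain from closing it is confined to dropout that depends on observed data, about 4–9% of slope shrinkage in the illustrative case. It would be wrong to claim that imputation cures the larger shrinkage seen when dropout depends on the unobserved 12-month value.

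**What to change.** In Proposed Data Analyses, choose one of two routes for the main arm contrasts, activity above all:

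1. Take them from the mixed model the plan already names, with baseline and all follow-ups as outcomes and arm means constrained equal at baseline; or
2. Keep baseline as a covariate and impute missing baselines in the main analysis.

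Report the complete-baseline model as the sensitivity analysis. Route 1 keeps everyone with any measurement, and its results match baseline adjustment when data are complete.

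Run the mediation regressions on the planned imputed datasets, with the earlier activity measurements in the imputation model, and report complete cases as sensitivity. State that this corrects bias only where dropout depends on observed data.

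The cost is a few sentences and modest programming, with slightly more complex reporting, chiefly for mediation. No new data are needed.

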**Methods:**

Small Steps for Big Changes is a 2-arm randomized controlled trial that will examine the effectiveness of combining brief exercise counseling with HIIT or MICT on adherence to moderate and vigorous exercise over 1 year. Cardiorespiratory fitness will be assessed at baseline, post intervention (2 weeks), and at 6- and 12-month follow-up. Physical activity behavior will be examined at baseline, post intervention, and 3-, 6-, 9-, and 12-month follow-up. The impact of the intervention on psychosocial outcomes pertinent to exercise adherence will be examined.

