## Methods

### Study Design

*Small Steps for Big Changes* is a 2-arm, parallel group randomized controlled trial comparing adherence to HIIT with MICT in individuals at risk of T2D. This single-center trial will be conducted at The University of British Columbia, Okanagan Campus. The design of the study and flow of participants is described in Figure 1. Participants in both conditions will receive a 2-week supervised physical activity intervention consisting of engagement in their randomized exercise modality and brief, targeted counseling. The physical activity counseling will be identical for both conditions. Follow-up assessments will occur at 3, 6, 9, and 12 months. The trial will aim to recruit 100 participants. The supervised training will be conducted in waves (10 waves with approximately 10 participants per wave). All participants will begin supervised training on a Monday. Reporting of this trial protocol follows the Standard Protocol Items: Recommendations for Interventional Trials statement. Future reporting of the results of this trial will follow the Consolidated Standards of Reporting Trials guidelines [41].

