### Participants

The study sample will consist of adults aged between 30 years and 65 years; who are physically inactive (ie, engage in 2 or less bouts of moderate and/or vigorous aerobic exercise per week in the last 6 months, assessed using the Godin Leisure Time Physical Activity questionnaire [42]); have a body mass index (BMI) between 25 kg/m^2^ and 40 kg/m^2^; and are cleared to engage in vigorous exercise (via the Physical Activity Readiness Questionnaire for Everyone [PAR-Q+] or further clearance by physician, if needed [43]).

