### Exercise Counseling

To assist participants with the transition to independent exercise and to promote long-term exercise adherence, participants in both conditions will receive a brief behavioral exercise counseling intervention built into the 2-week supervised training program. The counseling involves 10 minutes of one-on-one structured discussion at the end of each supervised exercise session, totaling 70 minutes over the 2 weeks. Participants will see the same counselor each session to bolster rapport. A detailed description of the BCTs used in the behavioral intervention and the social cognitive mechanisms they are hypothesized to target is reported elsewhere ([name] et al, unpublished data). Participants will receive a worksheet for each of the 3 home-based sessions, each reviewing specific behavior change constructs.

In summary, the key aims of the behavioral exercise counseling are to:

Enhance confidence to perform the exercise (ie, task self-efficacy): providing instruction on how to perform the behavior, opportunities to practice engaging in exercise, helping participants identify physiological cues associated with the assigned exercise intensity, sharing the success stories of similar individuals, and providing positive support.Increase confidence to self-manage exercise (ie, self-regulatory efficacy): providing opportunities to practice self-monitoring behavior, preplan exercise behavior, work through exercise barriers, and practice independent exercise.Increase awareness of the psychological and physiological outcomes associated with exercise engagement (ie, outcome expectations): through education and drawing on the experiences of similar individuals and of the participant throughout the 2-week intervention.

The counseling will follow a semistructured format, targeting specific psychological and behavioral constructs each session, while allowing the participants to share their questions and concerns. The content of the program, tools, and materials to be used; session description; and the underlying theoretical constructs are presented in Multimedia Appendix 2.

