## Discussion

The *Small Steps for Big Changes* program will be the first randomized trial to examine the efficacy of low-volume HIIT compared with traditionally prescribed MICT as a means of increasing long-term physical activity behavior in individuals at elevated risk of T2D. The impact of HIIT on cardiorespiratory fitness, physical activity adherence, and psychosocial outcomes will be directly compared with current exercise recommendations for this population (ie, moderate-intensity continuous exercise).

The authors acknowledge potential limitations in the proposed methodology. Specifically, exercise studies suffer from potential selection bias, which could impact the generalizability of the results. Furthermore, the considerable number of outcome measures may limit an individual’s willingness to participate. However, the number of outcome measures included in this study is similar to other exercise randomized controlled trials [76,77]. Generalizability of the findings may also be limited because of the study being conducted on a university campus, which may not reflect the environment of most individuals.

However, the findings from this study have the potential to make substantive contributions to understanding how different types of exercise protocol are tolerated and adhered to and the comparative health outcomes associated with these protocols. These findings could have significant implications for exercise recommendations provided for individuals at risk of diabetes.

In addition, this trial examines the effectiveness of a brief behavioral intervention designed to support the promotion of independent physical activity behavior through facilitation of self-regulatory strategies and efficacy beliefs. This intervention brings together theory and evidence in a carefully constructed intervention that will have the opportunity to examine the causal pathways from cognitions to exercise adherence. Together, the results of this trial have the potential to impact future public health campaigns designed to increase physical activity with individuals at risk of T2D.

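### With the same counselling in both arms and no untreated arm, change from baseline cannot show that the treatments or the counselling work; only HIIT versus MICT is identifiable

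*Protocol article*

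**What the plan says.** Study Design describes a "2-arm, parallel group randomized controlled trial comparing adherence to HIIT with MICT in individuals at risk of T2D" and states: "The physical activity counseling will be identical for both conditions". Exercise Counseling repeats that "participants in both conditions will receive a brief behavioral exercise counseling intervention built into the 2-week supervised training program", 70 minutes in all. The section on the self-monitoring application describes the app, reminders and monthly messages for all participants, with no distinction by arm. No untreated or uncounselled group appears anywhere.

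Proposed Data Analyses first gives mixed models with baseline as covariate, comparing HIIT with MICT on VO2 peak at 6 and 12 months and on accelerometry at 3, 6, 9 and 12 months. It then adds: "Mixed-effects regression using baseline and all other time points will be used to determine whether the treatments result in a significant change from baseline". All tests are at the 5% level.

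Sample Size reports that VO2 peak needs 15 per group. It then sets the final number, 41 per group raised to 50, on a within-group MVPA increase of 10 minutes per day with SD 16.

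The Abstract says the trial will "examine the effectiveness of combining brief exercise counseling with HIIT or MICT on adherence to moderate and vigorous exercise over 1 year". The Discussion says that "this trial examines the effectiveness of a brief behavioral intervention designed to support the promotion of independent physical activity behavior" and that the intervention gives the opportunity to "examine the causal pathways from cognitions to exercise adherence". Its limitations cover selection bias, the number of outcome measures and generalisability. They do not mention the lack of a control for counselling or for change over time.

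**The concern.** A factor that is the same in both arms has no effect that the randomised comparison can estimate. What is left for counselling, or for the programme as a whole, is the before-after change, and a before-after change has no control. A significant result says that activity or fitness differed from baseline. It does not say why.

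Other explanations are plausible here. Entrants must "engage in 2 or less bouts of moderate and/or vigorous aerobic exercise per week in the last 6 months", they answer advertisements aimed at people who want to become regular exercisers, and their activity is measured repeatedly. Some rise could occur with no programme at all.

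At stake is how the results are reported. A before-after finding could appear in the report of a randomised trial as evidence that the brief counselling, or the treatments as such, caused the change.

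**Working it through.** **1. What the design identifies.** For one outcome, let P_H and P_M be the effects of the HIIT and MICT programmes (exercise plus counselling, app and contacts) against no programme. Let D be the change that would have occurred anyway, equal in expectation in both arms by randomisation.

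- Expected change in the HIIT arm: P_H + D
- Expected change in the MICT arm: P_M + D
- Difference: P_H − P_M

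There are two observable means and three unknowns. The difference is free of D, but neither P_H nor P_M can be recovered. Splitting either into a counselling part and an exercise part adds another unknown and no further data.

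Suppose, for illustration, that both arms rise by 10 minutes per day. Then P = 10 with D = 0, P = 5 with D = 5, and P = 0 with D = 10 all fit equally well, and the HIIT − MICT difference is 0 in each. No sample size or model applied to these two arms separates the three cases.

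**2. The statements against this result.**

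| Statement | Quantity needed | Identifiable? |
|---|---|---|
| Between-arm mixed models (Proposed Data Analyses) | P_H − P_M | Yes |
| Whether treatments result in change from baseline (same section) | P_H and P_M separately | No |
| Effectiveness of the behavioural intervention (Discussion) | Counselling part of P | No |
| Effectiveness of counselling combined with HIIT or MICT (Abstract) | P_H and P_M, unless read as a comparison of the two | Only as a comparison |

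The same limit applies to mediation. The intervention effect on the mediators can only mean HIIT against MICT, not counselling against none.

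**3. The sample size.** Inputs from the Sample Size section: difference 10, SD 16, power 80%, P<.05 (taken as two-sided).

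- Two independent means: n = 2 × [16 × (1.960 + 0.842)/10]² = 40.19, so 41 per group. This reproduces the plan's figure.
- A true within-group (paired) t-test needs 23 if the correlation between visits is 0.5, where the SD of change is 16 × √(2 × 0.5) = 16. It needs 31 at correlation 0.3 and 15 at 0.7. The plan states 0.5 for VO2 peak only, so its use for MVPA is an assumption.

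So 41 is labelled within-group but equals the requirement for a between-arm difference of 10 minutes per day. With 41 per arm, power for that contrast is 80.8% (normal approximation) or 79.8% (t-test). With 40 per arm (50 less 20%) it is 79.8% or 78.8%. Limiting inference to the randomised contrast therefore calls for no larger sample, although the plan does not name 10 minutes as a between-arm target.

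**4. What the within-arm data can give.** With 41 per arm and SD of change 16, the 95% half-width is 1.96 × 16/√41 = 4.9 minutes per day. It is 5.8 at correlation 0.3 (SD of change 18.9) and 3.8 at 0.7 (SD of change 12.4). That describes the change; it does not attribute it.

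**The case against.** The best defence is that counselling effectiveness is not what this trial sets out to show. None of the listed Objectives asks for it, Study Design and the opening of the Discussion put HIIT against MICT, and the between-arm models come first in the analysis section. The Discussion sentence comes late and is an addition. All this stands. A reader might infer that the headline conclusion is that brief counselling works, or that the main analysis is compromised. The documents support neither.

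A reader might also put a number on the background change by a regression-to-the-mean formula and derive a false-positive rate for the within-arm test. That does not hold up. The formula applies when people are selected on the same measurement that serves as baseline. Here eligibility rests on a questionnaire and a 7-day recall interview, and the baseline accelerometer is worn afterwards. Some regression may remain, but its size cannot be derived from the documents. Participants were not selected on VO2 peak, so the argument does not carry over to the primary outcome. Season is a weak explanation at 12 months, which falls at about the same time of year as baseline.

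Nor does the text plan separate tests in each arm, so a contrast of one significant arm with one non-significant arm is not built into the plan. A model-based test of change is tolerable if it is not read causally; dropping p-values is a reporting preference.

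What the defence does not remove is the wording. The analysis section attributes change to the treatments, the Discussion claims effectiveness for a component common to both arms, and the final sample size is justified on the uncontrolled change. An analysis plan not shown here could not repair this, because the limit lies in the design.

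**Conclusion.** The point holds in this form: neither the counselling effect nor the effect of the combined programme is identifiable, and the document makes statements in Proposed Data Analyses and the Discussion that need them to be. This follows from identical counselling and the absence of an untreated or uncounselled arm, and rests on no numerical assumption.

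Its size cannot be given as a bias or an error rate. Background change is plausible, but the documents do not indicate how large it is.

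The randomised comparison of HIIT with MICT is unaffected, both for VO2 peak, the primary outcome, and for between-arm MVPA. The fault is in what may be concluded from the secondary before-after analysis, and it should be corrected before results are reported.

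**What to change.** - **Proposed Data Analyses:** limit causal and confirmatory inference to the randomised HIIT versus MICT contrast. Describe change from baseline within arms as estimates with 95% confidence intervals, and replace the wording that has the treatments producing the change.
- **Abstract and Discussion:** state that both modalities were delivered with the same counselling and that its effect is not estimable in this trial. Add the missing untreated or uncounselled control to the limitations.
- **Sample Size:** state that the within-group MVPA target supports a descriptive, uncontrolled estimate.

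The cost is wording in four places, with no new data or participants. Data collection ended in March 2017, so a further arm is no longer possible and narrowing the claims is the available remedy. The downside is a weaker statement about counselling.
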